##### Asthma-Related Quality of Life

Health-related quality of life will be evaluated using the Asthma Quality of Life Questionnaire (AQLQ) [33,34]. This questionnaire consists of 4 domains that assess the last 2 weeks: activity limitation, symptoms, emotional function, and environmental stimulation. The AQLQ score ranges from 0 to 7; the higher the score is, the better the quality of life. A difference of 0.5 points is considered clinically significant [35].

##### Body Composition and Anthropometric Indexes

Octopolar InBody 720 equipment (Biospace) will be used. The weight, fat mass, fat-free mass, visceral adiposity area, and skeletal muscle mass will be calculated. The InBody 720 uses 8 electrodes to assess body composition according to total body water, proteins, minerals, and fat mass. The contact points to connect the electrodes will be cleaned with an electrolytic cloth, according to the manufacturer’s instructions. Data will be electronically imported into Microsoft Excel using Lookin’Body 3.0 software (Biospace). Anthropometric data, including height, body weight (Filizola), abdominal, waist, and hip circumference, and waist-to-hip ratio will be measured according to standardized protocols [36,37]. BMI will be calculated by dividing body weight (in kg) by height (in m^2^) [38].

##### Anxiety and Depression

The Hospital Anxiety and Depression Scale (HADS) will be used to assess anxiety and depression symptoms [39]. The HADS is composed of 14 questions divided into 2 subscales, anxiety and depression (7 questions each). Each question ranges from 0 to 3, with a maximum score of 21 points for each subscale. In this study, a cut-off score (≥8) will be used to classify the presence or absence of symptoms of anxiety or depression [40].

##### Asthma Exacerbations

Asthma exacerbation is defined as an event in which a patient requires urgent action and needs to change the pharmacological treatment [41]. During this study, at least one of the following criteria will be used to define an exacerbation: the use of ≥4 puffs of rescue medication per 24 hours during a 48-hour period, a need for the administration of systemic corticosteroids, an unscheduled medical appointment, and either a visit to the emergency room or hospitalization [21,25,41].

##### The Behavioral Stage for Physical Activity

The assessment of “readiness to change” will be graded using a questionnaire to evaluate the following behavioral stages for physical activity: *Precontemplation*, *Contemplation*, *Preparation*, *Action,* and *Maintenance* [24,42]. The data will be presented in frequencies.

##### Barriers to Performing Physical Activity

Barriers to PADL practice will be assessed using a questionnaire that contains the most common barriers in adults [43,44]. The options to answer each question included: never, rarely, sometimes, almost always, and always, and each item score varies from 0 to 4. Higher scores indicate higher barriers.

### Sample Size Calculation

A minimum number of 17 individuals in at least one of the groups (responder or nonresponder) was established to detect a difference of 2500 (SD 2500) steps [45] in the primary outcome (α=5%, 1 – β=80%). A sample of 100 participants was established, considering the percentage of nonresponders (17%) as previously observed [5]. Clinical improvement in the ACQ score (≥0.5) [3,32] will be considered a secondary outcome.

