**Objective:**

This study aims to (1) identify the characteristics of adult responders and nonresponders with asthma to a behavioral intervention to increase physical activity and (2) evaluate the functional and clinical benefits in the medium term.

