### Statistical Analysis Planning

Individuals will be stratified as “responders” and “nonresponders” based on an increase of ≥2500 steps [45]. The Kolmogorov-Smirnov test will be used to assess data normality. Cluster analysis will be used to characterize the groups according to individual characteristics. Cluster analysis will be carried out in 2 stages: hierarchical analysis using the Ward method to determine the number of clusters and k-means analysis to group the clusters [46]. Comparisons of clinical, anthropometric, and psychosocial data obtained in the responder and nonresponder groups will be conducted using the 2-tailed *t* test or Mann-Whitney *U* test for continuous variables and the chi-square test for categorical variables. To determine the independent factors associated with the level of PADL (dependent variable, considering clinical control, smoking, obesity, anxiety, and depression as independent variables), multiple linear regression analysis (stepwise forward) will be used. The intra- and between-group comparison at baseline, short term, and medium term will be assessed using the 2-way ANOVA with repeated measures test. The significance level will be adjusted to 5% (*P*<.05) for all tests. If necessary, intention-to-treat analysis will be performed, as described earlier. SPSS Statistics (version 22.0; IBM Corp) will be used for statistical analysis. Data integrity will be monitored by regularly scrutinizing data files for omissions and errors. Participants will be given an anonymous study ID to protect confidentiality, and only study investigators will have access to the final trial data set.

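### The 80% power is for a step difference between groups that are themselves defined by step change, so it does not describe power for the main objective

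*Protocol article*

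**What the plan says.** The Abstract gives the first aim as to "identify the characteristics of adult responders and nonresponders with asthma to a behavioral intervention to increase physical activity". The Introduction repeats this as the main objective.

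The Sample Size Calculation section sizes the study on a different quantity. It states: "A minimum number of 17 individuals in at least one of the groups (responder or nonresponder) was established to detect a difference of 2500" steps (SD 2500) in the primary outcome, at "α=5%, 1 – β=80"%. It then sets the total at 100, citing a nonresponder share of 17% in a previous study. Outcome Measures defines the primary outcome as steps per day.

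The Statistical Analysis Planning section divides patients into responders and nonresponders "based on an increase of ≥2500 steps". Clinical, anthropometric and psychosocial data are then compared between the two groups; this "will be conducted using the 2-tailed *t* test or Mann-Whitney *U* test for continuous variables", with the chi-square test for categorical variables. The sample-size section gives no effect size for any of these characteristics.

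**The concern.** Steps define the groups, and steps are also the outcome on which the groups are to be shown to differ, with 2500 used for both. A power figure is useful when the difference might or might not exist. Patients who gained at least 2500 steps must have a larger mean gain than those who did not, whatever explains response.

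The question the study asks is whether asthma control, age, anxiety, depression or obesity differ between the groups. A reader who carries the 80% over to that question would be misled about how small a difference the study can find. The Discussion says the results may inform referral according to patients' profiles, so it matters whether a characteristic that shows no significant difference had a reasonable chance of showing one.

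The group-size condition has a separate fault. With 100 patients in two groups, one group always holds at least 50, so a minimum of 17 in at least one of them cannot fail. The calculation needs 17 in the smaller group.

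**Working it through.** **Inputs.** From Sample Size Calculation: difference 2500, SD 2500, alpha 5%, power 80%, nonresponder share 17%, N=100. From Statistical Analysis Planning: cut-off of 2500 on the increase in steps, and 2-tailed t tests. The sample-size section does not state sidedness; two-sided is assumed because the planned group comparisons are 2-tailed.

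**1. The plan's own figure.** The standardised difference is d = 2500/2500 = 1.0.
- Normal approximation: n per group = 2 × (1.960 + 0.842)² / 1.0² = 15.7, so 16.
- t test: 16.7, so 17 per group; power at 17 versus 17 is 80.7%.
- One-sided t test: 13.1, which does not match.
- Total: 17 / 0.17 = 100.

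Both stated figures reproduce. The 17 is the size of each group in a two-group t test with equal groups, and dividing by 17% shows that it was meant for the smaller group, the nonresponders.

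**2. What the grouping does to step change.** Assume that change is normal with SD 2500; the article does not say whether its SD is that of a change or of a level. If a share q lies below the cut-off, the difference in mean change between the two sides is SD × φ(z_q) / [q(1 − q)].
- q = 0.17: z = −0.954, φ = 0.2531; 2500 × 0.2531 / (0.17 × 0.83) = about 4,480 steps (1.79 SD). The group means are about 1,164 and 5,648.
- q = 0.50: φ = 0.3989; 2500 × 0.3989 / 0.25 = about 3,990 steps.

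In simulation with N=100, the t test on 8-week change rejected in 100% of runs.

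**3. How far this reaches.** The primary outcome is a level, so levels were simulated as well, with 17% nonresponders on average, equal SDs of 2500 at each visit, and the same correlation between any two visits (assumptions).

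| Comparison | Correlation 0.5 | Correlation 0.7 |
|---|---|---|
| 8-week change | 100% reject | 100% reject |
| 8-week level | about 94% | about 75% |
| 16-week level | about 5% | about 5% |

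Only the change score is fixed by the split.

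**4. What 100 patients give for the main objective.** Two-sided 5% t test on one continuous baseline characteristic. The smallest difference detectable with 80% power is approximately 2.802 × √(1/n₁ + 1/n₂) SD.
- 17/83: 2.802 × √(1/17 + 1/83) = 0.746; t-based 0.753.
- 50/50: 2.802 × √(1/50 + 1/50) = 0.560; t-based 0.566.

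| True difference | Power at 17/83 | Power at 50/50 |
|---|---|---|
| 0.5 SD | 46% | 70% |
| 1.0 SD | 96% | over 99% |

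**5. The split.** If the true nonresponder share is exactly 17%, the chance of at least 17 nonresponders among 100 is 54% (binomial). The share is itself uncertain: in the Introduction, 17% is the proportion who did not improve their physical activity level, not the proportion who gained fewer than 2500 steps.

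**The case against.** The strongest reply is that the circularity is narrower than it looks. The primary outcome is steps per day, and the plan also compares the groups at baseline and at the 16-week follow-up. A reader might infer that every step comparison between responders and nonresponders is settled in advance and that no null hypothesis remains. The documents do not support that. The 8-week level is strongly favoured by the grouping but not certain to differ, and under the assumptions in the working the 16-week level has a true null, rejected in about 5% of runs. Whether responders keep their gain is a question that the Discussion raises, and it is a genuine one.

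A reader might also infer that the sample size carries no information about the main objective. That too goes too far: 17 versus 83 gives 96% power for a 1-SD difference in any continuous characteristic. What remains is that the article makes no such argument and gives no reason to expect a difference of 1 SD in a characteristic. The 0.5 SD used here for illustration is not the protocol's either, so the detectable difference is the safer thing to report.

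The group-size condition may fairly be called a slip of wording, since the next sentence shows the intent. It should go, but it does not undermine N=100. Nor do the documents say that a nonsignificant characteristic will be declared irrelevant; that is a risk of interpretation.

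**Conclusion.** The point holds in this form: the stated 80% power belongs to a contrast that, on the 8-week change in steps, the grouping itself produces, and it does not describe power for finding characteristics that differ between the groups. The size of the built-in difference, about 4,480 steps at 17/83, depends on normality and on 2500 being the SD of change; that responders have the larger mean change depends on neither. For the main objective, N=100 gives 80% power for about 0.75 SD at 17/83 and 0.57 SD at 50/50, per characteristic and without adjustment for multiple comparisons.

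The arithmetic behind 17 and 100 is correct, and nothing here shows that 100 patients is the wrong number. The fault lies in the justification and in the empty group-size condition.

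**What to change.** Keep N=100 and rewrite the paragraph:

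- Remove the 80% power claim for a step difference between responders and nonresponders, together with the condition on at least one of the groups. Changing that condition to each group would not help: the claim it belongs to is going, and group size cannot be assured when response is an outcome.
- State what 100 patients detect for a continuous baseline characteristic with a two-sided 5% t test and 80% power: about 0.75 SD if the split is 17/83 and about 0.57 SD if it is 50/50. Add that power for 0.5 SD is 46% and 70% respectively.
- State that the split will be known only after the intervention, and that the 17% comes from a different definition of nonresponse, so the two splits show a range and are not a forecast.

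The cost is one rewritten paragraph and a less favourable stated figure. No extra patients and no change of analysis are needed.

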### Statistical Analysis Planning

Individuals will be stratified as “responders” and “nonresponders” based on an increase of ≥2500 steps [45]. The Kolmogorov-Smirnov test will be used to assess data normality. Cluster analysis will be used to characterize the groups according to individual characteristics. Cluster analysis will be carried out in 2 stages: hierarchical analysis using the Ward method to determine the number of clusters and k-means analysis to group the clusters [46]. Comparisons of clinical, anthropometric, and psychosocial data obtained in the responder and nonresponder groups will be conducted using the 2-tailed *t* test or Mann-Whitney *U* test for continuous variables and the chi-square test for categorical variables. To determine the independent factors associated with the level of PADL (dependent variable, considering clinical control, smoking, obesity, anxiety, and depression as independent variables), multiple linear regression analysis (stepwise forward) will be used. The intra- and between-group comparison at baseline, short term, and medium term will be assessed using the 2-way ANOVA with repeated measures test. The significance level will be adjusted to 5% (*P*<.05) for all tests. If necessary, intention-to-treat analysis will be performed, as described earlier. SPSS Statistics (version 22.0; IBM Corp) will be used for statistical analysis. Data integrity will be monitored by regularly scrutinizing data files for omissions and errors. Participants will be given an anonymous study ID to protect confidentiality, and only study investigators will have access to the final trial data set.

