The World Health Organization (WHO) recommends that adults perform 150 to 300 minutes of moderate-intensity aerobic physical activity weekly to achieve certain health benefits [8]. In addition, international guidelines [9] and GINA [1] classify, with A-level evidence, people with asthma who engage in regular physical activity to reduce cardiovascular risk and improve their quality of life [1]. A previous study found that a behavioral intervention to increase PADL improves clinical asthma control, sleep quality, and anxiety symptoms in adults with moderate to severe asthma [5]. However, 17% of the individuals did not improve their physical activity level, and 25% did not improve their clinical control after the intervention. Individuals with other chronic respiratory [10], cardiac [11], musculoskeletal [12], and neurological diseases [13] have also been classified as better or worse responders to specific interventions.

Thus, despite the benefits obtained by behavioral intervention aimed at increasing PADL in adults with asthma [5], it is necessary to know the characteristics of responders and nonresponders to guide the management in a more personalized approach. Moreover, the effects of this intervention were only assessed in the short term (immediately after the intervention), and the medium-term effects remained unknown. We hypothesize that the intervention might cause different effects according to the clinical characteristics of the individuals, including asthma control, age, anxiety and depression levels, obesity, and several comorbidities. Therefore, the main objective this prospective cohort study will be to identify the characteristics of adult responders and nonresponders with moderate to severe asthma to a behavioral intervention to increase PADL and evaluate the functional and clinical responses in the short and medium terms.

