### Outcome Measures

The primary outcome will be PADL (the number of steps per day) using an activity monitor (by actigraphy). Secondary outcomes will include clinical asthma control, quality of life, body composition and anthropometric data, anxiety and depression levels, asthma exacerbations, physical activity barriers, and behavioral stages for physical activity. This will be a single-blinded (outcome assessor) study in which assessments will be performed before, immediately after, and 16 weeks later.

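### Characteristics of response are tested across a 2500-step cut, and no stated analysis relates them to the size of the step gain

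*Protocol article*

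**What the plan says.** All references are to the protocol article. The main objective in the Introduction is to "identify the characteristics of adult responders and nonresponders with moderate to severe asthma to a behavioral intervention to increase PADL". The hypothesis there names asthma control, age, anxiety and depression, obesity and comorbidities. Under Outcome Measures the outcome is continuous: "The primary outcome will be PADL (the number of steps per day) using an activity monitor".

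Statistical Analysis Planning turns the change in that outcome into two groups: "Individuals will be stratified as “responders” and “nonresponders” based on an increase of ≥2500 steps [45". The characteristics are then tested across the groups: "Comparisons of clinical, anthropometric, and psychosocial data obtained in the responder and nonresponder groups will be conducted using the 2-tailed *t* test", with Mann-Whitney and chi-square as alternatives. The same section plans three further analyses:

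- a cluster analysis to characterise the groups;
- a two-way repeated-measures ANOVA within and between groups;
- a forward stepwise multiple linear regression with the level of physical activity as dependent variable and clinical control, smoking, obesity, anxiety and depression as candidate predictors.

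Sample Size Calculation gives the expected split: "A sample of 100 participants was established, considering the percentage of nonresponders (17%) as previously observed [5".

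**The concern.** Once the change is cut at 2500 steps, a gain of 2400 counts the same as a loss, and a gain of 2600 the same as a gain of 8000. The tests of characteristics see only which side of the line a patient fell on.

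The other analyses do not restore what is lost. The ANOVA is described as a comparison within and between groups. The cluster analysis is described without any test against step change. The stepwise regression keeps a continuous outcome, but as written it concerns level. A characteristic can go with a low level at every visit and have nothing to do with the gain, or the reverse.

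The section on Contribution and Clinical Applicability expects the responder profile to guide referral of patients. A moderate predictor missed for lack of power could be read as unrelated to response.

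**Working it through.** **Inputs from the protocol.** Sample Size Calculation: N = 100, 17% nonresponders, α = 5%, power 80%, and the aim "to detect a difference of 2500 (SD 2500) steps". Statistical Analysis Planning: two-tailed tests and the cut at 2500.

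**Assumptions, not in the protocol.** The change runs from baseline to week 8 and is roughly normal. It is linearly related to a continuous characteristic with correlation r. Since r is not given, a range is shown.

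**1. The protocol's own figure.** The standardised difference is 2500/2500 = 1.0. A two-sided t test at 5% with 80% power needs 16.7, so 17 per group (power 80.7% at 17 versus 17). Then 17/0.17 = 100. Both figures reproduce. They concern a difference in steps, the variable that defines the groups, and not a difference in a characteristic.

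**2. Information kept after the cut.** For a normal outcome cut at quantile p, with φ the standard normal density at z_p, relative efficiency = φ(z_p)² / [p(1 − p)].

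| Nonresponders | Efficiency | Information lost |
|---|---|---|
| 17% | 0.454 | 55% |
| 30% (or 70%) | 0.576 | 42% |
| 50% | 0.637 | 36% |

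To match the continuous analysis in 100 patients, the two-group test would need about 100/0.637 = 157 patients at 50:50, or 100/0.454 = 220 at 17:83.

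**3. Power, where the continuous test has 80%.** Power after the cut = Φ[(1.960 + 0.842) × √efficiency − 1.960].

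- 17:83: Φ(2.802 × 0.674 − 1.960) = Φ(−0.073) = 47.1%, a loss of 32.9 points.
- 50:50: Φ(2.802 × 0.798 − 1.960) = Φ(0.275) = 60.8%, a loss of 19.2 points.

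**4. Simulation.** N = 100, bivariate normal, 40,000 runs per setting; correlation test with the change versus two-group t test across the cut.

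| r | Full scale | Cut 17:83 | Cut 50:50 | Loss in points (50:50 to 17:83) |
|---|---|---|---|---|
| 0.10 | 17% | 10% | 13% | 4 to 7 |
| 0.20 | 52% | 27% | 36% | 16 to 25 |
| 0.275 | 80% | 46% | 60% | 20 to 34 |
| 0.30 | 86% | 52% | 68% | 19 to 34 |
| 0.40 | 99% | 78% | 91% | 7 to 21 |
| 0.50 | 100% | 94% | 99% | 1 to 6 |

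**5. How firm is 17:83?** The Introduction describes the 17% as the share whose physical activity level did not improve in the earlier study, without tying it to a 2500-step cut. Suppose, as an assumption, that the change has SD 2500.

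- For 17% to fall below 2500, the mean gain must be 2500 + 0.954 × 2500 = about 4885 steps.
- If the 17% instead means no gain at all, the mean gain is 0.954 × 2500 = about 2385 steps. Then Φ[(2500 − 2385)/2500] = Φ(0.046) = about 52% would fall below the cut.
- With a mean gain of 1000, about 73% would fall below it.

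The split could therefore be near even, or nonresponders could be the majority.

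**The case against.** **The responder contrast is the stated question.** The objective asks for the characteristics of responders and nonresponders, and the threshold carries a citation that cannot be checked here. A predictor of average gain need not be the best marker of who misses a threshold. This stands: it is a reason to keep the comparison and add to it, not to replace it.

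**A continuous regression is already planned.** A reader might infer that characteristics are compared only across the cut. The protocol does not support that, because the stepwise regression has a continuous outcome and covers most of the hypothesised factors. A fuller analysis plan might show that level there means change, or level after the intervention. As the article words it, however, change is not mentioned, no visit or baseline adjustment is given, and age and comorbidities are absent from the listed variables.

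**The losses are conditional.** A reader might take 20 to 34 points as a fixed cost to this trial. It is not: the loss is 4 to 7 points at r = 0.1 and 1 to 6 at r = 0.5. The upper end also needs the 17:83 split, which the protocol does not establish for this cut. The figures rest on normality, while the protocol allows Mann-Whitney for non-normal data.

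**The calculation uses the change, whereas the proposed model uses week-8 steps adjusted for baseline.** With baseline steps as covariate, the coefficient of the characteristic is the same whether the outcome is week-8 steps or the change, so the estimate still describes step gain. The power of the adjusted model itself was not calculated.

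**Conclusion.** The point holds in a limited form. The protocol states no analysis of characteristics against the size of the step gain, and its one continuous model does not fill that gap as written. Under approximate normality the loss of information is at least 36%, the figure at the most favourable split, and 55% at 17:83. The corresponding power loss of about 20 to 34 points applies to moderate associations, r about 0.28 at N = 100, and shrinks on either side.

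The protocol does not support the stronger conclusion that the responder analysis is wrong or should give way to a continuous one. The point is an inexpensive improvement to the main question rather than an error that invalidates the plan.

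**What to change.** In Statistical Analysis Planning, keep the ≥2500-step responder/nonresponder comparison, with the same definition, as the clinical contrast. Beside it, prespecify a regression of week-8 steps per day on each hypothesised baseline characteristic (asthma control, age, anxiety, depression, obesity, comorbidities), with baseline steps as covariate, in all patients. Report the difference in step gain with a 95% confidence interval. State that a nonsignificant responder comparison alone will not be read as absence of association.

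The cost is a few sentences and a few more regressions on measurements already scheduled, with no extra patients or visits. The small downside is a second set of P values, which refer to step gain rather than to the responder label.

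### The test rule has no class for ordered categories, so the five behavioural stages default to a chi-square test that ignores their order

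*Protocol article*

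**What the plan says.** The outcome section on behavioural stage grades readiness to change over five steps that run from Precontemplation to Maintenance. It adds, on reporting, "The data will be presented in frequencies". Outcome Measures lists stage among the secondary outcomes, and Table 2 schedules it at baseline, 8 weeks and the 16-week follow-up.

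Statistical Analysis Planning covers clinical, anthropometric and psychosocial data in the two response groups. It assigns the t test or "Mann-Whitney *U* test for continuous variables and the chi-square test for categorical variables". There is no third class for ordered categories, and stage is not mentioned by name. A repeated-measures ANOVA is named for comparisons over time, also without mention of stage.

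Sample Size Calculation gives "A minimum number of 17 individuals in at least one of the groups (responder or nonresponder") and says "A sample of 100 participants was established", on the basis of 17% nonresponders. That implies about 17 versus 83.

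**The concern.** A five-category item reported as frequencies is, under a two-class rule, a categorical variable. Followed as written, the rule sends stage to a Pearson chi-square test with up to 4 degrees of freedom. That test spreads its sensitivity over every possible pattern of difference and takes no account of the order of the stages.

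The order carries the information here. The intervention is built on the transtheoretical model, and the main objective is to find what distinguishes responders from nonresponders. The natural hypothesis is that nonresponders sit at earlier stages. With perhaps 17 patients in one group, there is little power to give away on that question.

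**Working it through.** **Inputs from the article.** Total 100; 17% nonresponders, so 17 versus 83; five stages; 5% level for all tests. Two-sided testing is taken from the wording for the t test ("will be conducted using the 2-tailed"). The 17% is the earlier study's share whose activity level did not improve, whereas this study defines response as a gain of at least 2500 steps, so the actual split may differ.

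**The plan's own figure.** The sample size is set "to detect a difference of 2500 (SD 2500) steps", which is a standardised difference of 2500/2500 = 1.0. The normal approximation gives 2 × (1.96 + 0.84)² = 15.7, so 16 per group. The two-sided t test gives 16.7, so 17 per group, with 80.7% power at 17/17. Then 17/0.17 = 100. Both stated numbers reproduce. The article gives no power for the stage comparison.

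**Assumptions needed for stage.** The stage distribution and the size of the shift are not in the article. A proportional-odds shift was assumed: the odds of being at or below each stage are OR times higher in nonresponders. Two tests were compared at the two-sided 5% level:

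- Pearson chi-square, Σ(O − E)²/E over occupied stages, df = occupied stages − 1.
- Mann-Whitney, z = (W − n₁(N + 1)/2)/√V, where W is the rank sum of group 1 and V = (n₁n₂/12) × [(N + 1) − Σ(t³ − t)/(N(N − 1))]; t is the number of patients tied at each stage.

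There were 20,000 simulated trials per scenario (Monte Carlo standard error at most 0.35 points).

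**Power at 17 versus 83, five equal stages, assumed distribution placed in the 83 responders:**

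| OR | Chi-square | Mann-Whitney | Loss (points) |
|---|---|---|---|
| 2 | 16.0% | 30.2% | 14.2 |
| 3 | 38.3% | 62.6% | 24.3 |
| 4 | 58.0% | 80.9% | 22.9 |

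**Range over five assumed five-stage distributions, same convention.** These include an early-stage one (30/35/25/7/3%) and a late-stage one (5/10/25/40/20%).

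| OR | 1.5 | 2 | 3 | 4 | 6 | 8 |
|---|---|---|---|---|---|---|
| Loss (points) | 2–7 | 9–18 | 17–30 | 16–33 | 9–22 | 4–14 |

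**Sensitivity.**

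- Which group holds the assumed distribution: with equal stages placed in the 17 nonresponders, power is 47.5% versus 63.0% at OR 3 (loss 15.5) and 68.8% versus 81.8% at OR 4 (loss 13.0).
- Three occupied stages at 15/35/50%, placed in the nonresponders: 51.6% versus 56.0% at OR 3 (loss 4.4) and 68.6% versus 73.5% at OR 4 (loss 4.9). Placed in the responders, the loss is up to about 8 points. Other three-stage distributions would give other figures.
- Split: over the same range of ORs the loss is about 1 to 28 points at 30/70 and about 0 to 21 at 50/50.
- Non-monotone differences: the order reverses. In two assumed cases, chi-square versus Mann-Whitney power was 44.5% versus 1.8% and 77.8% versus 12.0%.

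**Expected counts.** The expected counts in the smaller group add up to 17. With five occupied stages the mean is 17/5 = 3.4. Four cells at 5 or more would need at least 4 × 5 = 20, which exceeds 17, so at most three can reach 5 and at least two fall below it. In the scenarios run, 3 to 5 did. With three occupied stages the mean is 17/3 = 5.7; with a 50/50 split and even stages it is 50/5 = 10.

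**Type I error.** With no difference between groups, chi-square at 17/83 rejected in 4.7% to 5.5% of trials.

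**The case against.** The strongest reply is that the article never says stage will be tested by chi-square. Frequencies are an ordinary way to show ordinal data, grading implies order, and the analysis paragraph is a summary; the choice of test for one secondary variable could be left to a fuller plan. Part of this stands. A reader might infer that the plan declares the stages unordered, and the text does not support that: the assignment to chi-square is an inference. What remains is that the article does state a test rule, and that rule has no place for an ordered category other than the chi-square class.

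A reader might also take some single figure as the cost in power. The article fixes none: the loss moves with the stage distribution, the odds ratio, the split and the group in which the distribution is placed. Entry is restricted to inactive adults, so upper stages may be empty at baseline, which shrinks the loss.

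Finally, the low expected counts might be read as making the chi-square test invalid. That is not supported either. They require about 17 in the smaller group and all five stages occupied, and even then the simulated error rate stayed close to nominal.

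**Conclusion.** The point holds as a minor one. The stated rule lacks a class for ordered categories, and by default the five stages go to a test that ignores their order. If nonresponders tend towards earlier stages, this loses power against an ordinal test: roughly 2 to 33 points at 17 versus 83 with five occupied stages, under assumed proportional-odds shifts with OR 1.5 to 8. It is about 4 to 8 points at OR 3 to 4 in the three-stage case examined. Sparse cells are a secondary matter, with no demonstrated harm to the error rate. The advantage of an ordinal test depends on a broadly monotone shift. The primary outcome and the sample size are unaffected.

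**What to change.** Add one sentence to Statistical Analysis Planning: behavioural stage will be compared between responders and nonresponders with the Mann-Whitney test corrected for ties, or with a linear-by-linear trend test, in exact form if the table is sparse. Keep chi-square, or an exact test where expected counts are low, for unordered variables. Keep the frequency table as planned.

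The change needs no new data and no more patients, and the tests are standard. The price is lower sensitivity to a non-monotone difference, for example nonresponders clustering at both ends of the scale. The frequency table would still show such a pattern, but the test might not detect it.
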